#### List of statistical procedures

Assuring random assignment to groups, for this purpose, we need to test whether the observations differ in any of the time zero measurements. Indifference means there is no allocation bias.

T-test for each of the variables between SC and IC
Risk perceptionOutcome expectancySelf-efficacyESS – time zeroPSQI – time zeroEQ5D – time zeroSocial supportSocio-economic (ordinal) – chi-square test

In case of violation of the *t* test assumption (normality of the error term), Wilcoxon tests will be implemented.

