### Sample size {14}

A minimum sample size of 56 patients distributed in two groups is proposed for given α (0.01) and power (0.9), for 2 randomly assigned groups, intervention care (*n* = 28), standard care group (*n* = 28). Finally, assuming a maximum of 15% dropout, a total number of 64 patients is required.

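### Non-significant baseline tests between the arms cannot show that allocation was free of bias, as the protocol says they do

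*Protocol article*

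**What the plan says.** The Protocol article, List of statistical procedures, gives the purpose and the method in one sentence: "Assuring random assignment to groups, for this purpose, we need to test whether the observations differ in any of the time zero measurements". The conclusion to be drawn follows directly: "Indifference means there is no allocation bias".

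The method is "T-test for each of the variables between SC and IC". The list covers risk perception, outcome expectancy, self-efficacy, ESS, PSQI, EQ-5D and social support, with a chi-square test for socio-economic position. If normality fails, "Wilcoxon tests will be implemented". No significance level and no equivalence margin is given for these tests.

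Sample size {14} plans 28 patients per arm, and then adds: "assuming a maximum of 15% dropout, a total number of 64 patients is required". Sequence generation {16a} describes blocks of ten with stratification by OSA severity. Concealment mechanism {16b} describes a sealed opaque envelope held by the chief investigator.

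**The concern.** The protocol gives baseline p-values a task they cannot perform, for two separate reasons.

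- **Absence of evidence.** A non-significant result means only that the data are compatible with no difference. In arms of this size they are also compatible with sizeable differences.
- **Wrong question.** Under proper randomisation the null hypothesis of a baseline test is true by construction, and whatever difference appears is chance. Whether allocation could have been influenced is a matter of how the sequence was generated and concealed. Balance on a chosen list of variables cannot settle it.

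At stake is a sentence in the trial report declaring allocation free of bias on evidence that does not bear on it. The reverse is also possible: a chance difference could be read as a fault in a sound randomisation.

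**Working it through.** **Inputs.** 28 per arm (Sample size {14}); 32 per arm if all 64 recruited patients have baseline data; eight variables (List of statistical procedures). Assumptions: two-sided tests; alpha of 0.05, or 0.01, the only alpha in the article, which belongs to the sample size; true imbalances of 0.3 and 0.5 SD.

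**The plan's own figure.** There is none for the baseline tests. The planned 28 per arm cannot be re-derived either, because the article gives no effect size. Solved backwards with two-sided alpha 0.01 and power 0.9, it implies a standardised difference of (2.576 + 1.282) × √(2/28) ≈ 1.03. That is context only; the point does not depend on it.

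**Smallest observed difference that is significant**, t(1 − α/2; 54 df) × √(2/28), where √(2/28) = 0.267:
- alpha 0.05: 2.005 × 0.267 = 0.54 SD
- alpha 0.01: 2.670 × 0.267 = 0.71 SD

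So an observed gap of half a standard deviation would be read as no difference at either level.

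**Power of one t-test** (noncentral t, noncentrality d × √(n/2); for d = 0.5 and n = 28 this is 0.5 × √14 = 1.87):

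| True imbalance | n per arm | alpha 0.05 | alpha 0.01 |
|---|---|---|---|
| 0.3 SD | 28 | 0.20 | 0.07 |
| 0.5 SD | 28 | 0.45 | 0.22 |
| 0.3 SD | 32 | 0.22 | 0.08 |
| 0.5 SD | 32 | 0.50 | 0.27 |

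For 80% power with 28 per arm, the true imbalance must be about 0.76 SD at 0.05 or 0.94 SD at 0.01. These figures are per variable and apply to the seven t-tests, not to the chi-square test.

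**At least one significant result under perfect randomisation**, if the eight tests are independent:
- alpha 0.05: 1 − 0.95^8 = 0.337
- alpha 0.01: 1 − 0.99^8 = 0.077

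**The whole list as one rule.** The protocol looks for a difference on any of the variables. With one true imbalance of 0.5 SD, seven null variables and independence, the chance of some significant result is:
- alpha 0.05: 1 − 0.549 × 0.95^7 = 1 − 0.549 × 0.698 = 0.62
- alpha 0.01: 1 − 0.777 × 0.99^7 = 1 − 0.777 × 0.932 = 0.28

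At 0.05, the seven null variables alone give 1 − 0.698 = 0.30, so much of the 0.62 is chance flags on variables that are not imbalanced. The rule would still declare no bias in 38% of such trials at 0.05 and in 72% at 0.01.

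**The case against.** The best defence is that the sentence has no consequence. That largely stands. List of statistical procedures attaches no action to either result. Assessing the aims of the study specifies repeated measures ANOVA by group, and then regressions on psychosocial and socio-economic predictors, without reference to baseline p-values. A reader might infer that the tests decide which comparisons are adjusted or believed; the document does not say so.

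Three further objections also limit the point.

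- **Alpha and independence.** The 34% needs both an alpha of 0.05 and independent tests. At 0.01 it is 7.7%. The three SEMSA constructs come from one instrument, and ESS and PSQI both concern sleep, so positive correlation is likely and would lower either figure. The protocol also states only the direction from no difference to no bias; the false alarm arises if a reader applies the converse.
- **Single test or whole list.** The low power is per variable. It is tempting to say that the rule would usually miss a subverted allocation. At 0.05 that does not follow for a 0.5 SD imbalance, where some flag appears in about 62% of trials, and subversion affecting several variables would be flagged more often.
- **Untested variables and concealment.** AHI, age, BMI and neck circumference are recorded but not on the test list. That is no separate defect: baseline significance tests are unhelpful for any variable, and severity is already controlled by stratification. Nor does this point show that allocation is or will be biased. The strength of concealment is a different question, to be judged on the procedures themselves.

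None of this rescues the inference. At 0.01, where the false alarms mostly disappear, the chance of missing a real imbalance is larger.

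**Conclusion.** The concern holds as an error of inference with limited consequence. The protocol states, without qualification anywhere else in the article, that no difference on the baseline tests means no allocation bias. With 28 per arm, a single test misses a true 0.5 SD imbalance about 55% of the time at alpha 0.05 and 78% at 0.01. With 32 per arm it still misses about 50% and 73%. More basically, no sample size would make baseline tests a proof of unbiased allocation.

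The figures rest on assumed alphas and imbalances, and the family-wide ones on independence. The conclusion about the inference needs none of them. The harm is a false statement about allocation in the report, not an invalid comparison of adherence. The change should be made because it is nearly free and removes a wrong conclusion.

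**What to change.** 1. Delete the sentence equating no difference with no allocation bias, together with the baseline t, Wilcoxon and chi-square tests.
2. Present baseline data by arm descriptively, without p-values.
3. Rest any statement on allocation bias on the sequence generation and concealment procedures and on how they were carried out.
4. Include OSA severity, the randomisation stratum, in the adherence analyses whatever the observed balance. The ANOVA under Assessing the aims of the study names only the groups.
5. Adjust for the T0 score only in outcomes that have one: ESS, PSQI, EQ-5D and the SEMSA scales. Adherence is first measured at 3 months and has no T0 value.

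The cost is a small change of analysis wording and a few degrees of freedom: two for severity, if the strata are the three AHI grades given in the background. No new data are needed, and eight tests fall away.

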#### Assessing the aims of the study

In order to assess the aims of the study, we will test each of the repeated measures first by themselves using a repeated measures ANOVA controlling for groups:
Adherence – reported, times 3, 6, 18, 36 difference 3–6, 6–18, 18–36Adherence – objective, times 3, 6, 18, 36 difference 3–6, 6–18, 18–36ESS, time 6, difference 0–6PSQI, time 6, difference 0–6EQ5D, time 6, difference 0–6Risk perception, times 3, 6, difference 0–3, 0–6, 3–6Outcome expectancy, times 3, 6, difference 0–3, 0–6, 3–6Self-efficacy, times 3, 6, difference 0–3, difference 0–6, 3–6

Once we understand the trends in the data, we can construct multiple regressions for Adherence variables. These can be the final measures from time 6 or the differences between them and previous times, 0 or 3. In these models, we will use the Psychosocial variables and socio-economic as predictors, beyond the group classification.

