
At pre-treatment T(1), participants will undergo the initial fitting of the MAA and be provided instruction on use and care.

Both IC and SC groups will be called for follow-up at 3 (T2), 6 (T3), 18 (T4) and 36 (T5) months. Any problems that the patients might be experiencing regarding MAA use will be attended to at these appointments. In addition, data indicating adherence will be collected and evaluated at the appointments both subjectively and objectively by downloading the data from the sensor using dedicated software.

Furthermore, at T(2), participants will be asked to complete the SEMSA questionnaire, whilst at T(3), participants will need to complete the ESS, SEMSA, PSQI and EQ-5D questionnaires.

One-to-one interviews will be conducted 6 months into treatment with both (*n* = 5–10) compliant and non-compliant patients. It will comprise of questions, which will address the following topics:
Patient's awareness of risks and benefits of OSABarriers and facilitators of MAA therapyThe interviews will be conducted face-to-face, recorded, and transcribed by a third-party service (Essential secretary Ltd., UK). However, due to the COVID-19 pandemic, the interviews will take place online (Microsoft® Teams or Zoom cloud meetings) to ensure the participant’s safety. Although, if the participant is comfortable travelling, the interview can be carried out in a private seminar room. Inductive content analysis will be employed to describe the experiences of OSA and MAA therapy of compliant and non-compliant patients without imposing preconceived categories and names of categories to evolve from the data [49].

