### Outcomes {12}

#### Primary outcome

Adherence i.e. the number of hours the patient uses their appliance every night will be measured both objectively and subjectively at 3, 6, 18 and 36 months to assess the effectiveness of the interventions in enhancing adherence to MAA.

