### Participant timeline {13}

The participant timeline is found in Table 3.

**Table 3 Tab3:** Schedule of assessment

Assessment	Baseline T0	Pre-treatment T1	3 months T2	6 months T3	18 months T4	36 months T5
Questionnaires						
Epworth Sleepiness Scale (ESS)	X			X		
Self-Efficacy Measure for Sleep Apnea	X		X	X		
(SEMSA)				X		
Pittsburgh Sleep Quality Index (PSQI)	X			X		
EQ-5D	X					
Socio-Economic Questionnaire	X					
Social Support Questionnaire	X					
Age	X					
Gender	X					
Body mass index (BMI)	X					
Neck circumference	X					
Objective measure of adherence			X	X	X	X
Subjective measure of adherence			X	X	X	X
One-to-one interviews				X		

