## Statistical methods

### Statistical methods for primary and secondary outcomes {20a}

Both objective and subjective data of adherence i.e. duration of the usage of the appliance will be collected at 3, 6, 18 and 36 months will be analysed to assess the effectiveness of Intervention care in comparison with standardised care.

Comparison of pre- and post-treatment scores of ESS, SEMSA, PSQI, and EQ-5D, for both the groups, will aid in identifying significant differences in terms of improvement.

Statistically, evaluate the ability of the variables -self-efficacy, risk perception, outcome expectancy, social support and socio-economic position, to predict patient adherence at 3, 6, 18 and 36 months.

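### The predictor regressions offer a change in adherence from a time 0 that has no adherence value, leave the outcome to be chosen after the trends are seen, and name nothing beyond month 6 although prediction at 3, 6, 18 and 36 months is promised

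*Protocol article*

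**What the plan says.** All references are to the protocol article.

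- *Assessing the aims of the study*, timing: "Once we understand the trends in the data, we can construct multiple regressions for Adherence variables".
- Same section, outcome: "These can be the final measures from time 6 or the differences between them and previous times, 0 or 3".
- Same section, predictors: "we will use the Psychosocial variables and socio-economic as predictors, beyond the group classification". No visit is given for the predictor scores.
- *Statistical methods for primary and secondary outcomes {20a}*, scope: the psychosocial and socio-economic variables are to be evaluated for their ability "to predict patient adherence at 3, 6, 18 and 36 months".
- *Primary outcome*: adherence, defined as hours of appliance use per night, "will be measured both objectively and subjectively at 3, 6, 18 and 36 months".
- *Participant timeline {13}*, Table 3: the row "Objective measure of adherence" and the matching subjective row are marked at T2 to T5, with nothing at T0 or T1.
- *Trial design {8}*: "At pre-treatment T(1), participants will undergo the initial fitting of the MAA". T1 follows baseline T0.
- *Exclusion criteria*: patients who have used such an appliance before are excluded.

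**The concern.** The regressions serve a declared secondary objective: to identify indicators of adherence and turn them into a predictor model. Four features of the text work against that.

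1. One of the three outcome forms offered needs a baseline adherence value that cannot exist.
2. The outcome is to be settled once the data have been looked at. The reported significance of a predictor would then not carry its nominal error rate.
3. The forms named end at month 6, while the methods section promises prediction to month 36. Decline of adherence over years is part of the trial's own rationale, so the later times are not incidental.
4. Because no visit is fixed for the predictors, self-efficacy, risk perception and outcome expectancy from month 3 or 6 could be entered next to group. Those scores are taken after randomisation, and Table 1 lists the same constructs as targets of the intervention. A group coefficient adjusted for them is no longer the total intervention effect. A month-6 score used to predict month-6 hours may also reflect adherence rather than forecast it.

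**Working it through.** The plan gives no figure of its own for this point. Its only calculable figure is the sample size ("A minimum sample size of 56 patients distributed in two groups is proposed for given α (0.01) and power (0.9"), and nothing below depends on it except as a note on the significance level.

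**Step 1: is there a time-0 adherence?** Definition: hours of appliance use per night. First fitting: T1. Earlier use: excluded. Scheduled measurements: 3, 6, 18 and 36 months. So no value exists at time 0. If zero is entered for everyone, month 6 minus time 0 = month 6 − 0 = month 6, and the form adds nothing. The list of repeated-measures analyses in the same section agrees: its adherence differences are 3–6, 6–18 and 18–36, and differences from time 0 appear only for the questionnaires.

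**Step 2: count the outcomes.**

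- Offered: 3 forms (month 6, 6 minus 0, 6 minus 3) × 2 measures (reported, objective) = 6.
- The 2 forms from time 0 are undefined or redundant, so 6 − 2 = 4 usable outcomes remain.
- Promised in {20a}: 4 time points × 2 measures = 8, taking the promise to cover both measures.
- Promised and also named: month 6 on each measure, 2 of 8, or 1 time point of 4. A 3-to-6-month difference is not adherence at month 3.

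**Step 3: what choosing among the four does to the error rate.** Take one predictor with no true effect, tested two-sided at 5% on each form, with the most favourable form reported. Assumptions, none of them from the documents:

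- approximately normal test statistics and equal variance at months 3 and 6;
- correlation ρ between months 3 and 6 of 0.5 to 0.9;
- correlation r between reported and objective hours of 0.5 to 0.8, with cross-measure, cross-time correlation r × ρ.

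Within a measure, the correlation between the month-6 test and the difference test is (1 − ρ)/√(2 − 2ρ) = √((1 − ρ)/2). This is 0.50 at ρ = 0.5 and 0.22 at ρ = 0.9. The tests overlap but are far from identical. Simulation with 200,000 replicates per setting gave:

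| ρ | r | 2 forms, one measure | all 4 forms |
|---|---|---|---|
| 0.5 | 0.5 | 9.0% | 16.1% |
| 0.5 | 0.8 | 9.0% | 13.9% |
| 0.7 | 0.5 | 9.3% | 16.6% |
| 0.7 | 0.8 | 9.4% | 14.5% |
| 0.9 | 0.5 | 9.5% | 17.0% |
| 0.9 | 0.8 | 9.6% | 14.8% |

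For reference, independent tests would give 1 − 0.95² = 9.75% and 1 − 0.95⁴ = 18.5%. No significance level is stated for these regressions. At 0.01, the level used for the sample size, the four-form figure is 3.1–3.8%, again a little over three times nominal.

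**Step 4: predictor timing.** Table 3 schedules SEMSA at baseline, 3 and 6 months. The repeated-measures list treats the three SEMSA constructs at months 3 and 6, and their changes, as study variables. The regression sentence that follows does not restrict them to baseline. Later scores are therefore permitted, but not required.

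**The case against.** The strongest reply is that this is exploratory work on a secondary objective. Developing a predictor model normally begins with a look at the data, no confirmatory claim or threshold is attached to it, and a condensed article may leave detail to an analysis plan. Part of this stands: exploration is legitimate if it is labelled as such. But the text does more than stay silent. It states that the outcome follows from the trends, offers a form that cannot be computed, and names times that do not match the scope given in {20a}.

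The time-0 slip is also said to be harmless, because entering zero gives back the month-6 value. That is right as to the estimate. It remains an error in the text, and it makes the menu look longer than it is.

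Several stronger readings are tempting but not supported:

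- *The regressions stop at 6 months.* The wording on outcomes is permissive and excludes nothing, and the repeated-measures analysis of adherence runs to month 36. What can be said is that no regression outcome beyond month 6 is named.
- *Post-randomisation SEMSA scores will be entered with group, so the treatment effect will be biased.* The text only allows this. It never calls the group coefficient in these models the intervention effect; the intervention is assessed by the repeated-measures analysis.
- *A far larger error rate.* Five constructs on four outcomes would give 1 − 0.95²⁰ = 64%, or 18% at 0.01. That treats overlapping tests as independent and counts a false finding on any outcome, whereas the complaint is about choosing one outcome.

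**Conclusion.** The point holds as a fault in the specification of the secondary predictor analysis. The adherence change from time 0 is undefined or redundant. The outcome is left to a choice among four usable forms after the trends are seen. The forms named cover one of the four promised times. Predictor timing is open in a way that permits, but does not plan, post-randomisation scores.

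The size of the selection effect is roughly 14–17% instead of 5% for one null predictor, or about 9–9.6% if only one adherence measure is in play. Both ranges rest on the assumed correlations and on the most favourable form being reported, so they illustrate what the wording allows and do not predict what the analysts will do. The counting and the time-0 argument need no assumption beyond the protocol's own text. A reader might infer that the primary comparison of intervention with standardised care is compromised. It is not, because it does not use these regressions.

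**What to change.** - In the sentence on regression outcomes, replace the reference to previous times 0 or 3 with time 3 alone. This keeps the valid 3-to-6-month difference.
- Before any look at trends, name one lead regression outcome, for example objective hours at 6 months. List adherence at 3, 18 and 36 months as further pre-stated outcomes, or narrow the promise in {20a} to the times that will be modelled.
- State that the predictors are the baseline (T0) values of the SEMSA scales, social support and socio-economic position, plus group.
- Label as exploratory any model that uses later SEMSA scores and any outcome chosen after seeing trends.

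The cost is a few sentences and some freedom to explore, which the exploratory label largely restores. No data collection changes. The change has to be made before the trends are examined, because pre-specification cannot be recovered afterwards.

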Although initial subjective treatment adherence to MAA therapy is relatively high, it is declining over time. A phone-based survey of 69 patients with mild to moderate OSA prescribed MAA, reported a 32% adherence rate after 4 years of therapy, indicating a high level of non-adherence [12]. The study also suggested the prevention of barriers, associated with MAA therapy adherence, to improve the efficiency of the appliance and disease outcome. In a systematic review, Hoffstein et al. (2007) reported a wide range of (4–76%) adherence rates in the first year of appliance use and further studies have highlighted that adherence decreases with time [13]: 83% after 1 year [14] and 62–64% after 4–6 year [15, 16].

MAA adherence might differ depending on the type of the appliance, custom-made or ready-made, disease severity, and perhaps patient management [17]. In a recent systematic review, patient-reported adherence (6.4–7 nights per week and 5–6.3 h per night) and preference (*p* ≤ 0.001) were strongly associated to custom-made MAA in comparison to ready-made MAA [18]. Subjective side effects such as dry mouth, excessive salivation, tooth discomfort, muscle tenderness, and jaw stiffness, have never lead to treatment discontinuation [19–22]. In addition, tooth movement and occlusal changes have been seen in objective measurements after 1 to 4 years of follow-up, but these changes have not been reported as being related to treatment withdrawal [23–27].

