Research shows that adoption of a new health behaviour, like a new physical activity routine or adhering to a prescribed medication regimen, is a challenging endeavour involving a variety of social, emotional, and cognitive factors [29]. A multicentre study examined perceived effectiveness, self-efficacy and social support among 122 adult patients with OSA aged ≥ 65 years prescribed for MAA therapy [30]. With a 30% response rate (*n* = 39), the study reported low rates of perceived effectiveness, self-efficacy and social support highlighting the lack of self-efficacy, expectations for positive outcomes and social support experienced by the older patients in the sample. These findings are debatable as literature has identified psychological and social factors and cognitive perceptions as determinants of CPAP adherence, including patients’ risk perceptions, treatment outcome expectations, locus of control, and self-efficacy [31–33]. Another possible limitation of the study is that the questionnaires were mailed to the participants, who were only contacted once by the authors explaining the poor response rate. As a result, further research involving larger samples of men and women incorporating modes, which increase the response rate, is necessary to gain a better understanding of the patient's perception of MAA therapy. In turn, this understanding could be implemented for the development of interventions enhancing patient's adherence and experience to MAA treatment.

Interestingly, previous studies in the field of Sleep Medicine have featured an aspect of enhanced patient education ranging from telephone support to home visits, motivational enhancement, or augmented support [34, 35], which have been proven to effectively improve CPAP adherence when compared to usual care. Bakker et al. (2016) conducted a randomised controlled trial of CPAP use, with motivational enhancement (ME) or CPAP only in 83 participants, with moderate to severe OSA. The trial demonstrated a clinically significant increase in CPAP adherence in the intervention arm (CPAP with ME), supporting the use of a motivational enhancement approach to optimise the management of OSA [36].

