##### Secondary objectives

The secondary outcomes are as follows:
To identify the psychosocial and socio-economic indicators enhancing adherence of MAA in patients with OSA.Use of the indicators to develop a psychological and socio-economic predictor model.

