### Trial design {8}

This study is a single-centre, superiority, two-arm, parallel-group, individually randomised clinical trial, with 1:1 allocation, designed to test the effectiveness of stage-matched intervention in enhancing patient adherence to MAA therapy in patients with OSA. In addition, we plan to recruit patients with a confirmed OSA diagnosis, specifically referred for MAA therapy from secondary care.

Ethical approval was obtained from the Greater Manchester West Research ethics committee (REC ref: 19/LO/0972 and 19/NW/0391). Patients meeting the eligibility criteria will be provided with a patient information leaflet explaining the whole study. Interested patients will be asked to sign the informed consent, after which they will be randomly assigned into two groups- intervention care (IC) and standardised care (SC). Only the investigator and chief investigator (CI) will be aware of the participant’s allocation.

Participants will be provided with a sleep diary (Additional file 1) to record their hours of sleep and MAA wear-time, which will give a subjective record of the adherence (duration of usage of MAA). The TheraMon®, a micro-sensor included in the MAA design, will be used for the objective documentation of MAA adherence. TheraMon® calculates the actual wear time by measuring temperature every 15 min and then transforms this information into wear time when the temperature ranges between two specific values. In the present study, this range is defined as 28 °C to 38 °C, which includes the vast majority of intraoral temperature values observed in an individual under normal conditions.

At baseline (T0), part of the routine clinical subject demographics to be collected will include age, gender, body mass index (BMI), and neck circumference. The AHI will also be recorded during the initial screening. Following an oral examination, upper and lower alginate impressions will be taken along with the participant's bite. In addition, participants will be asked to complete the following questionnaires at T (0):
Epworth Sleepiness Scale (ESS)Self-efficacy measure for sleep apnoea (SEMSA) modified for oral appliancePittsburgh Sleep Quality Index (PSQI)EuroQol-5 Dimension (EQ-5D)Socio-economic position questionnaireSocial support scale

The above questionnaires will provide information concerning the participant’s daytime sleepiness, personality, quality of sleep, health-related quality of life, socio-economic status and social support, respectively.

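### The regressions for predictors of adherence do not name OSA severity, a collected stratification factor, so psychosocial coefficients could partly reflect severity

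*Protocol article*

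**What the plan says.** The terms of the predictor analysis appear twice in the protocol article.

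- Under Statistical methods for primary and secondary outcomes {20a}, the variables to be evaluated are "self-efficacy, risk perception, outcome expectancy, social support and socio-economic position, to predict patient adherence at 3, 6, 18 and 36 months".
- Under Assessing the aims of the study, multiple regressions for adherence follow the repeated-measures analyses, and "we will use the Psychosocial variables and socio-economic as predictors, beyond the group classification".

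These regressions serve two secondary objectives: "To identify the psychosocial and socio-economic indicators enhancing adherence of MAA in patients with OSA" and "Use of the indicators to develop a psychological and socio-economic predictor model".

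Severity appears in three other places.

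- Background and rationale {6a}: "MAA adherence might differ depending on the type of the appliance, custom-made or ready-made, disease severity, and perhaps patient management". The same section grades severity by AHI as mild (5–15), moderate (16–30) and severe (above 30).
- Trial design {8}: "The AHI will also be recorded during the initial screening".
- Sequence generation {16a}: OSA severity is the stratification factor for randomisation.

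Age is collected as well: "part of the routine clinical subject demographics to be collected will include age, gender, body mass index (BMI), and neck circumference". The background describes one survey of patients aged 65 or over that reported a lack of self-efficacy, "expectations for positive outcomes and social support experienced by the older patients in the sample". It then calls those findings debatable.

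**The concern.** Random allocation protects the comparison of intervention care with standardised care. It does not protect the coefficients of self-efficacy, risk perception, outcome expectancy, social support or socio-economic position, which patients bring with them or develop during follow-up. If severity is related to one of these scores and also to wear, a model without severity gives part of severity's effect to the score.

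The first secondary objective is worded in explanatory terms, as indicators that enhance adherence. A score reported on that basis could be a proxy for severity and could then be chosen as a target for later interventions. The trial treats severity as important enough to stratify on at allocation, but does not name it in the models where non-randomised predictors are interpreted.

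**Working it through.** **No figure to reproduce.** The plan gives no effect size, correlation or variance for the predictor regressions. The only documentary input is the sample size of 56, stated under Sample size {14}. Everything else about magnitude below is an assumption.

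**1. Model terms, side by side.**

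| Variable | Named in {20a} predictor list | Named in the regressions | Collected | Other role in the protocol |
|---|---|---|---|---|
| Five psychosocial and socio-economic variables | yes | yes | yes | secondary endpoints |
| Group | no | yes | yes | randomised |
| OSA severity (AHI) | no | no | yes | stratification factor; may affect adherence |
| Age | no | no | yes | low predictor scores in one older sample |
| Sex | no | no | yes | none linking it to adherence or to the predictors |

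**2. Possible bias.** Standardise all variables. Let r be the correlation of a psychosocial predictor with severity, and b the effect of severity on adherence. Suppose the predictor has no direct effect. If severity is omitted, the expected slope of the predictor is r × b instead of 0.

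**3. False-positive rate.** This was simulated with a single predictor, 20,000 replicates and a two-sided test at 0.05 (assumed, since the protocol sets no level for these regressions).

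| r | b | bias r × b | N = 56 | N = 64 |
|---|---|---|---|---|
| 0.1 | 0.2 | 0.02 | 5.1% | 5.1% |
| 0.2 | 0.3 | 0.06 | 7.1% | 7.4% |
| 0.3 | 0.3 | 0.09 | 10.1% | 11.0% |
| 0.4 | 0.4 | 0.16 | 21.8% | 24.4% |
| 0.5 | 0.4 | 0.20 | 31.7% | 35.9% |

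Hand check of the middle row at N = 56: the expected test statistic is about 0.09 × √56 = 0.67. The upper-tail probability beyond 1.96 − 0.67 = 1.29 is about 0.099, and the opposite tail adds about 0.004, giving roughly 10%. With severity in the model the expected slope is 0 and the rate returns to the nominal 5%.

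**4. Cost in degrees of freedom at N = 56.** Socio-economic position is counted as one slope.

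| Model | Slopes | Residual df (56 − slopes − 1) | Patients per slope |
|---|---|---|---|
| As named: five predictors + group | 6 | 49 | 9.3 |
| + continuous AHI | 7 | 48 | 8.0 |
| + continuous AHI + age | 8 | 47 | 7.0 |
| + three severity grades + age | 9 | 46 | 6.2 |

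**The case against.** Four arguments stand against the point.

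**The text does not exclude covariates.** The article says which variables will be used as predictors and that regressions can be constructed. It is a condensed account, and a fuller protocol or analysis plan could add adjustment terms. This stands, so it would be too strong to say that the models contain only these terms. What can be said is that both places that list the terms leave severity out. Naming a collected stratification factor is a concrete improvement on the stated model.

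**Confounding is not shown.** A reader might infer that the documents establish it for AHI, age and sex. They do not. Severity is linked to adherence, with a hedge, but not expressly to any psychosocial score. Age is linked to the scores only, through a survey with no younger comparison group and a 30% response, which the protocol itself doubts. Sex is linked to neither; it appears only in a call for larger samples of men and women. Each path has at most one documented side, so confounding is possible and no more.

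**The aim is partly prediction.** The secondary endpoint and {20a} speak of predicting adherence, and for pure prediction an unadjusted association is a legitimate quantity. This stands for the predictor model in the second objective. It does not cover the first objective, whose wording is explanatory.

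**The size rests on assumptions.** At the mild end of the range the inflation is essentially nil. This stands, which is why the whole range is shown.

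A reader might also suspect the comparison of the arms. Nothing here biases it, because allocation is random and stratified by severity.

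**Conclusion.** The point holds for OSA severity. The named regression terms leave out a variable that the trial collects, stratifies on and suspects of influencing adherence, while the objective asks an explanatory question about non-randomised predictors. Age is a weaker second candidate, and the documents give no basis for requiring sex.

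The consequence runs from negligible to material: about 5%, 10% or 32% false positives for a null predictor at N = 56, depending on correlations that the documents do not give. The figures assume one predictor at a time, linear effects and a two-sided 0.05 test. This is a cheap improvement to a secondary analysis. It is not a flaw in the primary comparison.

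**What to change.** Under Assessing the aims of the study, state that every predictor regression will include baseline OSA severity as a fixed, pre-specified term. It can enter as continuous AHI (1 degree of freedom) or, if the grades in the background are used, as mild, moderate and severe (2 degrees of freedom). Add age as a second-priority covariate. Sex need not be a required term. Report the psychosocial and socio-economic coefficients adjusted for these terms.

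Under Secondary objectives, replace *enhancing* with *associated with*.

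The cost is about two sentences and no new data. With continuous AHI and age, slopes rise from 6 to 8 and residual degrees of freedom fall from 49 to 47 at N = 56, a small loss of precision. No shrinkage method is needed for this change.
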